#### Analysis of phase I: pilot study I and pilot study II

Quantitative assessments and qualitative focus groups will be completed by consumers of My MFG after each MFG treatment session during the pilot studies to assess for palatability, feasibility, and technical issues. Likert-scale measures will be developed to allow consumers to rate aspects of each My MFG component for issues of palatability, feasibility, and technical issues. Scores below predefined cutoffs on these assessments, indicating concerns/problems, will be identified and used to refine the My MFG application. These scores will also serve as discussion points for the weekly post-session focus groups. Additionally, the weekly post-session focus groups will allow for consumers to provide feedback on all aspects of the My MFG application. The combination of weekly post-session assessments by consumers and weekly focus group discussions will allow for ongoing feedback on specific issues of palatability, feasibility, and technical issues while also allowing consumers to provide open feedback to further improve My MFG to meet consumer’s needs.

### Phase II: small-scale pilot randomised controlled trial

A small-scale pilot randomised controlled trial will be conducted to further understand feasibility, utility, and palatability, determine whether a “signal” can be detected, and to evaluate/refine the study protocol.

### Setting and recruitment

Participating outpatient mental health clinics in the New York City area will serve as sites for this study. Providers at the participating clinics will receive information about the proposed study and will have printed materials to provide to their clients about participation in the proposed study. Potentially eligible youth and their families (based on an intake diagnosis of ODD and CD made by clinical service providers) will be informed of the study by their providers (step I) and then, if the family is interested in learning more about the study, contacted by a member of the research staff (step II). In phase II, informed consent/assent will be completed by the family, which provides study details as well as specify the possibility of being selected for the MFG-alone or MFG plus MY MFG conditions via random assignment. If the youth and family is screened as eligible, and consent/assent is given, then study staff will contact the project director (blind to family information) who will assign the family to one of the two study conditions based on predetermined sequence based on random permutation calculation.

#### Inclusion criteria

Families will be included if they meet the following criteria: (1) youth between the ages of 7 to 13 years and an accompanying adult primary caregiver available to participate in the research and intervention activities; (2) English-speaking youth and adult caregiver; and (3) youth meeting criteria for DBD via standardized assessment procedure.

#### Exclusion criteria

Children will be excluded if there is evidence of psychosis. In addition, if the youth or adult caregiver presents with emergency psychiatric needs that require services beyond that which can be managed within an outpatient setting (e.g., hospitalization, specialized placement outside the home), active intervention by clinic and research staff to secure what is needed will be made. Children will not be excluded if they participate in other psychosocial or pharmacological interventions.

#### Treatment assignment and sample size rationale

Families will be assigned on a 1:1 basis to MFG alone (*n* = 40) or MFG plus My MFG (*n* = 40) (see Fig. 2 CONSORT flowchart) via predetermined sequence based on random permutation calculation by the project director, who is blind to family information. Both treatment conditions will run in parallel within each participating clinic. Sample size will be determined based on previous randomized controlled trial data suggesting that a sample size of 40 participants per condition would provide a meaningful difference in homework completion between those that are typically highly engaged and those that are less engaged.

**Fig. 2 Fig2:**
[figure not shown]
CONSORT flowchart

### Interventions

#### Multiple family group

Multiple family group (MFG) is a 16-week service delivery strategy that was guided by a manualized protocol. Each group included six to eight families, composed of identified youth, their adult caregiver(s), and sibling(s) between the ages of 6 and 18. As a foundation, MFG takes a common elements approach by identifying essential components from the empirical literature regarding core effective practices for treating DBDs, represented as the 4Rs (i.e., rules; responsibility; relationships; respectful communication) and factors related to family engagement in mental health services, represented as 2Ss (stress and social support. Each of the 16 sessions that focused on one of the 4Rs and 2Ss and proceeded with the following processes: (a) creating social networks; (b) information exchange/homework review; (c) group discussion regarding the skill; (d) individual family practice; and (e) homework assignment.

#### Multiple family group plus MY MFG

MFG plus MY MFG treatment condition has the same format, content, processes, and methods as MFG except that the homework process (homework review/homework assignment) is conducted through the My MFG application.

#### Measures

Data will be collected at baseline, pretreatment, at each session, and at post-treatment. See Table 1 for the data collection tools and timing of the collection of each measure. My MFG usage data (e.g., frequency, duration of use, which components used, etc.) will also be collected directly from servers throughout treatment.

**Table 1 Tab1:** Outcome measures for pilot randomised controlled trial phase

Domain	Measure	Reporter	Time of assessment
Homework process; homework quantity and quality	Homework rating scale-II [9]	Parent and clinician	Every session
Homework process	Homework adherence and competence scales [9]	Independent observer	Every session
Attendance	Session attendance	Clinician	Every session
Consumer satisfaction and feedback	Treatment attitude inventory [40] Feedback questionnaire Group and individual consultancy meeting	Parent; target child; therapist	Postreatment

#### Primary and secondary aims

The primary aim will be to obtain summary statistics of the key outcomes (quality of the design, do, and review phases, quality of homework completed), to determine usage of the My MFG application, and to identify challenges and barriers for uptake of My MFG application. An additional primary aim will be to determine the feasibility of the study protocol. Secondary analyses will compare MFG-alone to MFG plus My MFG on key homework process outcomes. The following hypothesis for this phase includesGreater quality of the “design” and “do” process rated by clinicians, parents, and independent coders. As My MFG is being developed to specifically address the design and do process, we hypothesize that clinicians, parents, and independent coders will rate the quality of these two processes to be high. We also hypothesize that MFG plus My MFG, compared to MFG-alone, will result in significantly better design and do process outcomes.Greater quantity and quality of homework assignments rated by clinicians and parents. Given aim #1 and hypothesis #1, we hypothesize that the quantity and quality of homework completed will be high for the MFG plus My MFG group. We also hypothesize that MFG plus My MFG, compared to MFG-alone, will result in significantly better scores on homework adherence and quality measures.Greater quality of the “review” process as rated by clinicians, parents, and independent coders. Given aim #2 and hypothesis # 2, we hypothesize that the review process during the MFG plus My MFG condition will be rated high by families (based on improved adherence to and quality of homework completed) as review of homework requires that homework be completed in a high-quality manner. Low rates and quality of homework limits opportunities for effective review. We also hypothesize that MFG plus My MFG, compared to MFG-alone, will result in significantly better scores on the review process.Greater satisfaction with treatment as rated by the parent, target child, and clinicians. We hypothesize that families and clinicians in the MFG plus My MFG condition will have high levels of satisfaction with the treatment process, given that the goal of My MFG is to enhance autonomous motivation, competency, and relatedness while enhancing the process of homework during MFG. We also hypothesize that MFG plus My MFG, compared to MFG-alone, will result in significantly higher satisfaction with treatment.

Additional primary aim: An additional primary aim will be to determine the feasibility of conducting the RCT protocol. Specific aims include whether the study protocol will allow for:Recruitment of 80 participantsRetention of 80 % of the sampleEfficient training of MFG facilitatorsEfficient data collection

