
#### Phase I: pilot study II

A second pilot study of MFG plus the revised My MFG will then be conducted to gather information from a different user group (six to eight families) who had not experienced the transformation of the prototype application. Feedback from study participants as well as MFG clinicians will be collected on an ongoing manner during MFG to rapidly revise, refine, and provide updated My MFG components/processes during the course of treatment while also finalizing My MFG prior to conducting a phase II small-scale pilot randomized controlled trial. Specifically, the objectives of the pilot II will be to:Determine if the revised prototype is palatable for consumers. Do consumers (i.e., families) find the content/methods in My MFG helpful in supporting homework? Are there aspects to homework support that is insufficiently addressed in My MFG? What new content/methods can be incorporated to further support homework? Do consumers like using My MFG?Determine if the revised prototype is feasible for consumers. Do consumers (i.e., families) find My MFG easy to implement daily? What are the challenges to implementing My MFG consistently?Determine if the revised prototype if technically sound for consumers. Do consumers (i.e., families) find My MFG easy to navigate? What are the challenges in programming My MFG for use? What are modifications, if any, to further improve navigation of My MFG? Do consumers find the steps to personalize My MFG easy to implement?Determine if the revised prototype is palatable and feasible for MFG Facilitators. Do MFG facilitators utilize My MFG in assigning and designing homework in MFG groups? What are the challenges in utilizing My MFG in assigning and designing homework? Do MFG Facilitators utilize My MFG in reviewing homework in MFG groups? What are the challenges in utilizing My MFG in reviewing homework? What are the challenges in integrating My MFG into practice in their clinical setting? What modifications, if any would facilitators recommend in improving My MFG so it aligns better to MFG and better supports the homework process?Determine the most efficient and effective manner to train and support MFG facilitators in learning and implementing My MFG into MFG groups. Does the revised training meet the needs of facilitators in learning and implementing My MFG into MFG? What recommendations do facilitators have to improve training?

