Secondary analyses will focus on between group (group: MFG plus My MFG and MFG-alone) X 2 (time: pre-treatment and post-treatment) repeated measures multivariate analysis of variance (MANOVA) to address homework quantity and quality at each session, average homework quantity and quality across all sessions, and quality of the design, do, and review processes. Alpha-inflation correction procedures will not be used for subsequent contrasts given the exploratory nature of the study. Follow-up analyses will include calculation of effect size by subtracting the MFG plus My MFG group mean from the MFG-alone group mean and dividing by the pooled standard deviation of the groups. Effect size data will be an important indicator of a “signal” that My MFG may be improving the homework process given the relatively small sample size of this study. Independent sample *t* tests will be used for determining differences between treatment conditions on consumer satisfaction to treatment. It is important to state that the results of these secondary analyses will be treated with caution given the small sample size of the RCT.

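### Clinicians who know the arm rate homework design and review that they themselves deliver, and these ratings count towards the between-arm hypotheses 1 and 3 without being separated from the other raters

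*Protocol article*

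**What the plan says.** All references are to the protocol article.

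- **Primary and secondary aims, hypothesis 1 (design and do).** The heading lists clinicians, parents and independent coders as raters. The text expects that "clinicians, parents, and independent coders will rate the quality of these two processes to be high" and that My MFG, compared with MFG alone, "will result in significantly better design and do process outcomes".
- **Same section, hypothesis 3 (review).** The heading refers to the "process as rated by clinicians, parents, and independent coders", and the text predicts that My MFG "will result in significantly better scores on the review process".
- **Measures, Table 1.** Parent and clinician complete the Homework rating scale-II at every session. An independent observer scores the homework process at every session on separate adherence and competence scales.
- **Multiple family group plus MY MFG.** The one stated difference between arms is that "the homework process (homework review/homework assignment) is conducted through the My MFG application".
- **Phase I: pilot study I and pilot study II.** The objectives treat facilitators as the people who design, assign and review homework. One asks: "Do MFG facilitators utilize My MFG in assigning and designing homework in MFG groups". A parallel question covers review.
- **Data analyses.** The secondary between-group analysis covers "quality of the design, do, and review processes". It names no deciding rater and no rule for disagreement, makes no alpha correction, and treats the effect size as an indicator of a signal. Its stated reason for caution is the small sample.

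**The concern.** For design and review, the clinician scores their own work and knows whether the new tool was used. A clinician trained on the app who expects it to help may score the same work higher in that arm. Such a shift goes in one direction, so averaging over 16 sessions does not remove it, and caution on grounds of sample size does not address it.

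The between-arm part of this pilot is meant to show whether a signal exists that would support a larger trial. If a clinician-rated difference enters that judgement on the same footing as the observer's, the signal may partly reflect how clinicians view their own practice.

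The point is confined to design and review. The do process is carried out by families, and in hypothesis 2 the clinician rates the family's homework. Clinicians know the arm there too, but they are not grading themselves.

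**Working it through.** **The chain in the text**

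1. Clinicians are named raters of design and review (hypotheses 1 and 3).
2. Clinicians deliver design and review. This is inferred from the Phase I facilitator objectives.
3. Clinicians know the arm. This is inferred from the description of the My MFG condition; a clinician who runs homework through the app cannot be unaware of it.
4. Both hypotheses make a between-arm superiority claim.
5. The analysis of design, do and review quality does not say how the three sources are kept apart or combined.

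The article gives no figure for rater bias, so there is nothing to reproduce. What follows is an illustration.

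**Inputs**

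- n = 40 per arm (Treatment assignment and sample size rationale).
- n = 32 per arm, from the 80% retention target: 0.80 × 40 = 32 (Primary and secondary aims).
- Assumed: true effect 0; clinician scores shifted upwards by b SD in the app arm only; two-sided 5% test; independent families.

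**Clinician score tested alone (two-sample t test)**

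The noncentrality is b × √(n/2), with 2n − 2 degrees of freedom. For n = 40, √20 = 4.472 and the critical value is 1.99 (78 df). For n = 32, √16 = 4 and the critical value is 2.00 (62 df). The table gives the probability of a significant result favouring My MFG.

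| Shift b (SD) | Noncentrality, n = 40 | Probability, n = 40 | Noncentrality, n = 32 | Probability, n = 32 |
|---|---|---|---|---|
| 0 | 0 | 2.5% | 0 | 2.5% |
| 0.2 | 0.89 | 14% | 0.80 | 12% |
| 0.3 | 1.34 | 26% | 1.20 | 22% |
| 0.4 | 1.79 | 42% | 1.60 | 35% |
| 0.5 | 2.24 | 60% | 2.00 | 50% |

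A normal approximation gives 14% to 61% and 12% to 52% over the same range.

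**How the rater rule changes this (n = 40, b = 0.5, parent and observer scores unbiased)**

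- *Any one of three independent ratings suffices:* 1 − (1 − 0.598) × 0.975² = 0.62.
- *All three must agree:* 0.598 × 0.025² = 0.0004.
- *The three ratings are averaged on equal SD scales:* the shift in the mean is 0.5 / 3 = 0.17 SD of a single rating. The SD of the average is √((1 + 2r)/3), where r is the correlation between raters. In SDs of the average, the shift is 0.17 at r = 1, 0.17/0.816 = 0.20 at r = 0.5 and 0.17/0.577 = 0.29 at r = 0.
- *The three ratings enter as joint outcomes in a multivariate test of the arms.* The article names a MANOVA but does not say that raters enter this way. The noncentrality is 20 × b² × c, with c = 1 at r = 0 and c = 1.5 at r = 0.5, on 3 and 76 df. For b = 0.2, 0.3, 0.4 and 0.5 the test rejects in 10%, 17%, 28% and 42% of trials at r = 0, and in 13%, 24%, 40% and 60% at r = 0.5, against 5% nominally.

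The result therefore runs from almost no effect to a large one, depending on a rule that the article does not give.

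**The case against.** The strongest reply is that clinicians are one of three informants. A reader might infer that self-appraisal alone can deliver the results predicted in hypotheses 1 and 3. The documents do not support that. Parents and an independent observer rate the same processes, and clinician inflation does not change their scores. It would settle a hypothesis only if a clinician-rated difference counted by itself, which the article neither says nor excludes. This part of the reply stands.

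Other points on that side:

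- **The comparative sentences name no rater.** This is true, and the explanation of hypothesis 3 speaks of families rating review highly. But the hypothesis headings list clinicians with the others for exactly these outcomes.
- **A rule for combining raters may belong in the full plan.** This is fair for the rule itself. What the article does fix is that clinician ratings of their own work count as evidence.
- **Some premises are inferred.** The items of the clinician scale are not shown, expectation of benefit is assumed, and the article does not say whether the same clinicians lead both arms. These limits stand.
- **The percentages rest on assumed inflation and a clinician-only t test.** This is correct. They also ignore clustering within groups of six to eight families. They illustrate the mechanism and do not estimate its size in this trial.
- **The contrast is secondary, exploratory and described as underpowered.** This is also correct, and it limits how serious the point is.

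**Conclusion.** The point holds in limited form. Unmasked self-ratings of design and review are listed as evidence for between-arm hypotheses 1 and 3. Self-appraisal can create a difference on the clinician-rated scale and can contribute to a joint or pooled test. It leaves the observer and parent scores unmoved.

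The range of about 14% to 60% (n = 40), or about 12% to 50% (n = 32), applies only if the clinician score is tested alone, the inflation is 0.2 to 0.5 SD, families are independent and there is no true effect. Averaging three raters would cut the raw shift to a third. Because the contrast is secondary and exploratory, this is a worthwhile, inexpensive improvement; it does not threaten the primary descriptive aims.

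**What to change.** In Primary and secondary aims and in Data analyses:

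1. Base the between-arm comparison and effect size for design and review on the independent observer scale already scored every session.
2. Analyse each rater source separately, with parent ratings as supportive evidence.
3. Report clinician ratings of design and review by arm as descriptive self-ratings that do not count towards hypotheses 1 and 3. Keep clinician ratings of homework quantity and quality, where the family is being rated.
4. Acknowledge that parents, and probably observers, can also see the arm. The change removes self-rating from the comparison but does not remove knowledge of the arm.

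The cost is analysis wording only, since all these ratings are already planned for collection. The downside is that one of three informants no longer counts as evidence in an exploratory contrast. The article's status section says that Phase II data are being coded, cleaned and analysed, so the rule should be fixed, if still possible, before arm comparisons are seen. Otherwise it should be labelled as set afterwards.

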#### Data analyses

Given that the pilot RCT is underpowered to detect differences between groups, our primary analyses will focus on descriptive summary statistics (e.g., means and standard deviation with confidence intervals). Specifically, summary statistics will be compared to established cutoffs on measures. This approach will allow for direct comparison of study summary statistics to established summaries allowing for assessment of various aspects of the DADR homework process (i.e., design, do, and review phases, quality of homework completed). Summary statistics of quantity of homework completed will be directly compared to our previous studies of MFG [9]. Moreover, completion of the measures every session will also allow for determining how each component of the My MFG application is affecting the homework process over time and for identifying key content and processes that may require further development. Collectively, this primary data analytic plan will determine the extent to which the proposed My MFG application affects key aspects of the homework process and allows for gathering of information to further refine the My MFG application.

We will gather information through the feedback questionnaire as well as post-treatment group and individual collaborative consultancy meetings regarding My MFG content, (parents, children, and clinicians) in order to further refine My MFG. We will also utilize My MFG usage data via servers as probes to obtain further information from participants regarding My MFG. The data from these sources will allow us to further understanding patterns of use (e.g., identify patterns of low usage over treatment; identify underutilized content, etc.), consumer challenges (processes, facilitators, and barriers to uptake from participants in using the My MFG application), and allow for further suggestions for refining the My MFG application.

We will also analyze feasibility and effectiveness of the study protocol through ongoing feedback from research staff and MFG facilitators. Information gathered from MFG facilitator/research staff will assist in understanding barriers to implementing the RCT study protocol (i.e., recruitment, retention, facilitator training, and data collection).

Secondary analyses will focus on between group (group: MFG plus My MFG and MFG-alone) X 2 (time: pre-treatment and post-treatment) repeated measures multivariate analysis of variance (MANOVA) to address homework quantity and quality at each session, average homework quantity and quality across all sessions, and quality of the design, do, and review processes. Alpha-inflation correction procedures will not be used for subsequent contrasts given the exploratory nature of the study. Follow-up analyses will include calculation of effect size by subtracting the MFG plus My MFG group mean from the MFG-alone group mean and dividing by the pooled standard deviation of the groups. Effect size data will be an important indicator of a “signal” that My MFG may be improving the homework process given the relatively small sample size of this study. Independent sample *t* tests will be used for determining differences between treatment conditions on consumer satisfaction to treatment. It is important to state that the results of these secondary analyses will be treated with caution given the small sample size of the RCT.

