#### Tools to support the development of autonomous motivation

##### *Push elements*

Families enter data to trigger timely text and audio reminders of significant milestones, reasons for implementing homework, and inspirational messages.

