##### *Triage and feedback*

Using information collected during setup and the weekly check-in with questions about family goals, use of MFG skills, levels of stress and social support and other risk or protective factors, My MFG will provide links to relevant My MFG resources. An example of what would happen if a participant is prompted and then accepts support: many parents experience stress at managing a child’s behavior at a specific time in the day (e.g., getting ready for bed). My MFG will remind (push-in) families at selected times (e.g., 30 min before bedtime) of what skills to use, offer MFG stress management exercises, or connect to online peer support from other members of the MFG group. Triage and feedback is intended to derail the automatic punitive and reactive family interactions and parenting discipline strategies often observed in families of youth with DBDs which maintain the disruptive problems experienced by the youth (and family) by providing the family with just-in-time, tailored coping supports and reminders to implement MFG homework skills when and wherever they may be needed. My MFG will help families focus on developing the 4Rs of MFG while goal setting will augment the quality of the homework implementation.

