#### Social support services (relatedness)

##### *Discussion groups*

Participants can exchange emotional support and information with others assigned to their MFG group via online support groups. They can share their progress in achieving My MFG goals and ask questions of both group participants and facilitators.

All of the tools that will be included lay self-determination theory over the DADR model of homework implementation, providing tools that motivate and engage, improve competence, or provide social support for the client during the critical do process. Tools can be customized during the design phase of the homework process and modified during the review phase of the homework process during the MFG group. The game can be adaptive to families via simple initial tasks and leveling-up to more difficult tasks that are related to more difficult to adopt behaviors.

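### The primary plan says session ratings will determine how each My MFG component affects homework, but the design contrasts only the whole application with none and cannot separate component effects

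*Protocol article*

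**What the plan says.** The sentence at issue is in the primary part of Data analyses: "completion of the measures every session will also allow for determining how each component of the My MFG application is affecting the homework process". It goes on to say that this will help pick out content and processes needing more development.

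Other sections of the protocol article fix what the data can show:

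- **Allocation** (Treatment assignment and sample size rationale): the article says that "Families will be assigned on a 1:1 basis to MFG alone", where 40 are planned, with another 40 in the arm that adds the application.
- **Difference between arms** (Multiple family group plus MY MFG): the app arm is the same as MFG "except that the homework process (homework review/homework assignment) is conducted through the My MFG application".
- **Components** (the tool descriptions under Designing My MFG): push elements, gamification and goal setting, questions and answers, triage and feedback, and discussion groups. They are presented as one set: "All of the tools that will be included lay self-determination theory over the DADR model of homework implementation".
- **Use of components**: for push elements, "Families enter data to trigger timely text and audio reminders". For triage, the example describes what happens "if a participant is prompted and then accepts support". For the tools generally, "Tools can be customized during the design phase of the homework process and modified during the review phase".
- **Measures** (Measures, Table 1): at every session, the Homework rating scale-II, the homework adherence and competence scales, and attendance. Satisfaction and feedback are collected at post-treatment. Server logs record which components are used.

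**The concern.** To determine how each component is affecting homework is a causal claim made component by component. It needs either component-level assignment or, at the least, component-level outcome data with a credible way to deal with who uses what. The protocol describes neither.

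At stake is the refinement of the application before a larger trial. If a session-by-session reading is presented as showing what a component does, content may be kept or changed on the strength of a pattern that has other explanations. Those include general family engagement, several components being used together, the skill covered that week, and changes to the app. Data analyses asks for caution only about the secondary analyses, so this primary-plan statement carries no caveat.

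**Working it through.** The protocol gives no figure for this claim, so there is nothing to reproduce. The check sets the claim against the design.

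**1. What randomisation identifies.** Two arms give one contrast, the whole application versus none. Five groups of tools are described. The number of component effects identified by randomisation is 0.

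**2. What the session measures can distinguish.** The Table 1 instruments rate homework quantity and quality and the homework process. The aims separate design, do and review. Those are stages of homework, and no instrument is listed as scoring a particular component. Phase I differs here: under Analysis of phase I, consumers rate aspects of each component after each session. Table 1 lists no such every-session rating for Phase II. Completing the listed measures at each session therefore cannot by itself tell components apart.

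**3. What the server logs add.** They are component-level, but Data analyses uses them as prompts for participant feedback and to describe patterns of use. No link to the session ratings is stated.

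**4. What a link would show if it were made.** Only associations, for four reasons found in the document:

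- Use depends on family input, acceptance and customisation (Push elements, Triage and feedback, Discussion groups).
- Tools may be modified during homework review (Discussion groups), so past homework can shape later exposure.
- In the app arm "the homework process (homework review/homework assignment) is conducted through the My MFG application", so app use and homework activity are tied together.
- Each of the 16 sessions is devoted to one of the 4Rs or 2Ss (Multiple family group), and app content is to be updated often (Gamification/goal setting). Change over sessions therefore mixes component, topic and app version.

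**5. Illustration under assumed inputs.** The conclusion does not depend on it. Suppose every true component effect is zero. Let general engagement correlate r_u with use of a component and r_y with the homework score, and split families into users and non-users at the median. The expected difference in homework is 2 × √(2/π) × r_u × r_y = 1.596 × r_u × r_y SD.

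- r_u = 0.3, r_y = 0.3: 1.596 × 0.09 = 0.14 SD (simulation 0.146).
- r_u = 0.7, r_y = 0.5: 1.596 × 0.35 = 0.56 SD (simulation 0.556).

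Precision is low as well. Within 40 app families, at two-sided 5% and 80% power, ignoring clustering and dropout, the smallest detectable difference is (1.960 + 0.842) × √(1/n1 + 1/n2):

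| Users / non-users (assumed) | Smallest detectable difference |
|---|---|
| 20 / 20 | 0.89 SD |
| 10 / 30 | 1.02 SD |
| 8 / 32 | 1.11 SD |

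The whole-arm contrast of 40 versus 40 gives 0.63 SD on the same formula, and the protocol already calls that contrast underpowered.

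**The case against.** The strongest reply is that no component-effect analysis is planned. The primary aims are summary statistics, app usage, barriers to uptake and feasibility. None of the four hypotheses concerns a component, and every planned test is by arm. Feedback questionnaires and consultancy meetings already inform refinement, and the Discussion speaks more softly of content that appears not to work well. This is a pilot ahead of a larger trial.

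Much of that stands, and it rules out some stronger readings:

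- **A biased regression is planned.** A reader might infer that homework will be regressed on component use, so that a tool favoured by struggling families would look harmful. No such model is described, so that harm is possible but not shown.
- **Refinement rests on session ratings alone.** It does not. Usage data and qualitative feedback are already part of it.
- **All components are known to be supplied together, with use wholly self-chosen.** No single sentence says so. It is inferred from the tool descriptions, which date from the Phase I design, and the app was revised afterwards. Nothing contradicts it, and no component-level assignment is described.
- **A bias of known size exists.** The documents give no correlations, so any figure rests on assumed ones.

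The reply does not rescue the sentence itself. It asserts a property that the design lacks, in the primary plan, without a caveat. A fuller analysis plan could not supply that property, because the allocation and the session measures are already fixed.

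**Conclusion.** The point holds as a correction to a stated claim. The two-arm comparison can inform the effect of the application as a package. The every-session measures cannot determine what each component does, and randomisation identifies none of the component effects. This rests on the described two-arm allocation, on the Table 1 measures, and on the absence of any component-level assignment in the article.

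It is modest in scale. No planned test, sample size or arm-level result is affected. What changes is how session-by-session findings may be interpreted when content is chosen for further development. The SD figures above show only that confounding could matter under assumed correlations, and they are not estimates for this trial.

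**What to change.** Replace the sentence in Data analyses with a statement to this effect: session ratings in the My MFG arm, alongside server-logged component use, will be described over time as exploratory, hypothesis-generating associations that cannot be attributed to individual components. Decisions on refining content will rest on these descriptions together with the usage data and qualitative feedback already planned. Extend the existing caution about the secondary analyses to this part of the primary plan.

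Optionally, component use in the interval before a session can be set against that session's rating, if the server logs are time-stamped (an assumption, since the article does not say). This would reduce confounding without removing it. It should stay descriptive, given about 40 app families treated in groups of six to eight. No particular model is needed for the correction. If component effects are wanted, a later trial could randomise components.

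The cost is wording only, with no new data. Current status of the study says that Phase II data were still being coded, cleaned and analysed, so the restriction can be applied in the analysis and reporting.
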